### Telerehabilitation system

The CUIDATE group will identify impairments of participants at baseline assessment. The aims based on weekly improvements will be set to facilitate the final goal. After each training session there will be feedback between the participant and the CUIDATE group to change or improve any exercise or activity. This feedback will allow to us to select adequate exercises and levels of difficulty. As a result, a modifiable personal training will be assigned to each one focusing on cardio-respiratory, mobility, and endurance performance through online system rehabilitation (using written instructions, HD videos, and audio files).

### Checking through e-CUIDATE

Participants will have three sessions per week during the 8-week period through e-CUIDATE. We will check that assigned sessions are being done properly each week through a control platform. Also, comments about doubts and suggestions will be written by participants after performing their sessions through e-CUIDATE. They will receive feedback (through text messages in their profiles in e-CUIDATE) about these comments before attending the following session. If they have a webcam they will also be able to receive feedback via this videoconferencing facility.

### Telephone calls

The telephone calls will be made by the CUIDATE group. The aim of these calls will be to solve any problems of carrying out the training sessions and to check levels of satisfaction and improvement. Also, messages of encouragement will be given to stimulate adherence to the program.

### Instant messaging through e-CUIDATE

Changes about assigned exercises will be provided by us. More messages of support and encouragement will also be received via this medium. Participants will use instant messaging to advise of any change in training days.

### Videoconference facility through e-CUIDATE

The videoconference facility will be available three times per week with a set schedule through Wormhole Web Conference and Skype software (Microsoft corporation, Redmond, Washington).

A single point of contact between patients and therapists will be located in university facilities and staffed by two full-time researchers. This will ensure that all patients receive standardized and comparable feedback and advice.

### Follow-up at 8 weeks

Post-intervention assessment will be made to check on aims achievement. Support and encouragement will be given to follow with training sessions self-sufficiently because all participants will continue to have access to their profiles in e-CUIDATE.

### Control group/usual care

The control group will receive a dossier of written information with brief general recommendations about stress management and improving physical fitness. These recommendations will be handed in at the beginning of the study. The dossiers will contain similar information to those of the telerehabilitation group but with a single written support. After completion of this study, for ethical compromise of the CUIDATE group, control participants will be given the opportunity to participate in a telerehabilitation program. These data will be not used in this research project.

### Monitoring with accelerometers

Participants of both groups (telerehabilitation and control group) will wear accelerometers (tri-axial motion sensor) at baseline, 8 weeks, and 24 weeks to know the lifestyle and habits of breast cancer survivors at different stages of the study.

### Sample size

The estimated sample size was determined for the primary outcome variable, that is, overall HRQoL using EORTC QLQ-C30 version 3.0 [26]. According to previously reported data [57] a minimally important difference of this HRQoL instrument is 5 to 10 points. Assuming that telerehabilitation increase HRQoL in breast cancer survivors respect control group we can detect differences of at least 5% with a power of 90% and an α of 0.05 with two groups (telerehabilitation and usual care group) of 36 participants assuming similar standard deviation of approximately 7 points. We will assume a maximum loss at follow-up of 10% [58]. We will recruit a total of 80 breast cancer survivors (that is, one intervention group and one usual care group of 40 persons each). Figure 1 shows the flow diagram of the study participants.

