### Assessment

#### Primary outcome measure

##### Quality of life

*The European Organization for Research and Treatment of Cancer Quality of Life Questionnaire Core 30* (EORTC QLQ-C30) *version 3*.*0*[26]: QoL will be assessed using EORTC QLQ-C30. This is one of the most widely-used instruments for measuring QoL in cancer patients. The questionnaire includes both multi-item scales and single-item measures. These are composed by five functional scales, three symptom scales, a global health status/QoL scale, and six single items; the scores have to be averaged and transformed linearly to obtain a range of score from 0 to 100 with higher score meaning a great response level [27].

*The European Organization for Research and Treatment of Cancer Breast Cancer*-*Specific Quality of Life questionnaire* (EORTC QLQ-BR23) [26]: It is a breast cancer module of EORTC QLQ-C30. This module contains 23 items assessing disease symptoms, side effects of treatment, body image, sexual functioning, and future perspective. All items are rated on a four-point scale ranging from 1 (not at all) to 4 (very much). The scoring procedure of the breast cancer module is the same as the EORTC QLQ-C30 [27]. The reliability has been found high to moderate (Cronbach´s α ranged between 0.46-0.94) [28].

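### The sample-size paragraph does not state sidedness; under a two-sided 0.05 test its inputs give about 85% power, not 90%, and the target is in percent where its basis is in points

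*Protocol article*

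**What the plan says.** The protocol article's Sample size section bases the calculation on one score: "The estimated sample size was determined for the primary outcome variable, that is, overall HRQoL using EORTC QLQ-C30 version 3.0". It takes the effect size from the literature, where "a minimally important difference of this HRQoL instrument is 5 to 10 points". It then claims that "we can detect differences of at least 5% with a power of 90% and an α of 0.05 with two groups" "of 36 participants assuming similar standard deviation of approximately 7 points". A 10% loss to follow-up takes 36 to "one intervention group and one usual care group of 40 persons each", 80 in total.

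Three other statements bear on the reading:

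- The power sentence opens with a direction: "Assuming that telerehabilitation increase HRQoL in breast cancer survivors respect control group".
- The Quality of life section says the questionnaire scores are "transformed linearly to obtain a range of score from 0 to 100".
- The Data analysis section names ANCOVA as the main analysis. Its covariates are time since diagnosis, age, tumor stage and type of surgery, and effects are to be reported for the group by time interaction. No one-sided test is mentioned.

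**The concern.** A reader who puts the printed inputs into the usual two-sided formula does not get 36 per arm. The document gives no sidedness that would explain the gap. The target also changes unit within the paragraph: the minimally important difference and the SD are in points, but the detectable difference is a percentage.

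At stake is how a null result will be read. The trial presents itself as having a 10% chance of missing a true 5-point effect, the lower end of its own minimally important range. Under a two-sided test at SD 7 that chance is about 15%. The loss-to-follow-up step is correct, so any shortfall in 36 carries straight through to the total of 80.

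**Working it through.** **Inputs, all from the protocol article.** Difference 5 (taken as points on the 0 to 100 scale), SD 7, alpha 0.05, power 90%, 36 evaluable per arm and 10% loss (Sample size); scale range (Quality of life). Sidedness is not given, so both cases are shown.

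**Loss to follow-up.** 36 / 0.9 = 40 per arm, 80 in total. This reproduces.

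**Sample size for 90% power**, n per arm = 2 × [SD × (z_alpha + z_power) / difference]²:

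- Two-sided: 2 × [7 × (1.960 + 1.282) / 5]² = 41.2, so 42. The t-test needs 43.
- One-sided: 2 × [7 × (1.645 + 1.282) / 5]² = 33.6, so 34. The t-test needs 35.

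The stated 36 is not the two-sided result. It lies one or two above the one-sided result.

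**Power with the stated numbers.** The standard error of the difference at 36 per arm is 7 × √(2/36) = 1.650, so the standardised effect is 5 / 1.650 = 3.03.

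- Two-sided, normal: Φ(3.03 − 1.96) = 85.8%.
- One-sided, normal: Φ(3.03 − 1.645) = 91.7%.

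| Evaluable per arm | Two-sided, normal | Two-sided, t | One-sided, normal | One-sided, t |
|---|---|---|---|---|
| 36 | 85.8% | 84.8% | 91.7% | 91.2% |
| 40 (no loss) | 89.1% | 88.4% | 93.9% | 93.6% |

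**Other routes to 36, two-sided normal formula.**

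- 85% power with SD 7: 2 × [7 × (1.960 + 1.036) / 5]² = 35.2, so 36.
- 90% power with SD 6.5: 2 × [6.5 × (1.960 + 1.282) / 5]² = 35.5, so 36. The t-test power for this case is 89.6%.

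**Difference detectable with 90% two-sided power at 36 per arm, SD 7.** (1.960 + 1.282) × 1.650 = 5.35 points; 5.42 by the t-test.

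**Recruitment for 90% two-sided power.** 42 / 0.9 gives 47 and 43 / 0.9 gives 48 per arm, 94 to 96 in total, against 80 stated.

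**The unit.** On a 0 to 100 scale, 5% of the range is 5 points, and it is the 5-point reading that brings n near 36.

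**The case against.** The best defence is that the protocol never says two-sided. Its power sentence is directional and so is the hypothesis under Objectives. A one-sided 0.05 test gives about 91% power at 36 per arm, so on that reading the 90% is delivered. The ANCOVA in Data analysis is not described as two-sided either; that is the conventional reading, not the document's text. This much stands, and it is why the 85% must be stated conditionally. A reader might infer that the claimed power is simply not delivered; the document does not support that without the condition. Still, a direction assumed for the effect does not specify a one-sided test, none is named, and the usual ANCOVA F test is non-directional.

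The SD is only approximate. A value of about 6.5 reproduces 36 under a two-sided normal formula, so one cannot conclude that 36 must have come from a one-sided test. Rounding can equally go the other way: an SD of 7.5 would give about 80% power.

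Covariate adjustment could raise power. However, the protocol gives no correlation to support this, the sample-size paragraph does not claim it, and the listed covariates do not include the baseline score.

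A reader might also take the 5% as a relative change in the mean score and infer far lower power. The document gives no mean score, and the sentence before sets the scale in points, so this is a slip of unit and does not change the calculation. Nor does the document give any basis for trying much larger SDs.

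**Conclusion.** The paragraph is wrong as written and should be fixed. Sidedness is missing. Under the conventional two-sided 0.05 test, the printed inputs support a claim about five percentage points lower than the one made. The conclusion rests on a two-sided test, an SD of 7 and a 5-point target with no gain from covariates.

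The practical effect is modest. The difference detectable with 90% power moves from 5 to about 5.4 points, still at the low end of the 5 to 10 point range that the protocol cites. No bias or loss of error control follows.

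**What to change.** In Sample size, state that the test is two-sided, replace the percentage with 5 points, and restate the claim along these lines: 36 evaluable per arm give about 85% power (two-sided 0.05, SD 7) for a 5-point difference, or 90% power for about 5.4 points.

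If a one-sided 0.05 test was intended, say so there and make the Data analysis section match. If the SD actually used was nearer 6.5, print that value.

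The cost is wording only. No extra patients are needed; the downside is a slightly less favourable stated power. Keeping the 90% claim for 5 points under a two-sided test at SD 7 would instead mean recruiting 94 to 96 women rather than 80.

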**Figure 1 F1:**
[figure not shown]
Flow diagram showing the recruitment of patients.

### Randomization and blinding

We allocated patients to a telerehabilitation program or control group in five randomization cycles, using computer-generated numbers (EPIDAT 3.1, Xunta de Galicia). The sequence was entered into numbered opaque envelopes by an external member and they were opened after completion of the baseline assessment. For ethical implications, those participants allocated to the control group, who finished the period of 6 months for the current study, were invited to receive the intervention when last outcome measurement was carried out. The researcher in charge of randomly assigning participants will not know in advance what treatment the next participant would receive and will not participate in assessment. Assessment staff will be blinded to the participant randomization assignment. No changes in assignment will be possible from the staff involved in the telerehabilitation program.

### Data analysis

Mean and standard deviation will be used to represent the variable scores at baseline and different follow-up measurements. Study population will be characterized using different descriptive statistics parameters. In a first step, we will analyze possible differences between groups at baseline using a one-way analysis of variance for continuous data (or equivalent statistical approach in the case of non-parametrical data) and Chi-square for categorical data. For the main analysis we will use an analysis of covariance (ANCOVA) to assess the effects of intervention on study variables. Time since diagnosis, age, tumor stage, and type of oncology surgery treatment will be used as covariates. To complete the analysis we will report effect size and level significance attending to interaction effects (group × time).

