### Research design and methods

A randomized controlled trial will be conducted with assessments at baseline, 4 weeks and immediately after intervention (at 8 weeks). Follow-up measurements will be carried out 24 weeks after the end of the 8-week intervention period, giving a total trial data collection period of 32 weeks. The assessments will be performed on 2 separate days to avoid fatigue in the patients. The study assessment schedule is shown in Table 1.

**Table 1 T1:** Study assessment schedule

**Assessment**	**Baseline**	**Follow****-****up**	**Post****-****intervention**	**Detraining**
		**(4 weeks)**	**(8 weeks)**	**(24 weeks)**
Informed consent	X			
*Day 1 testing*				
Sociodemographic data	X			
Anthropometric data, pressure/rate heart	X		X	X
Training on the treadmill	X			
Lymphedema	X		X	X
*Day 2 testing*				
Piper Fatigue Scale-revised	X	X	X	X
Trail Making Test	X		X	X
Auditory Consonant Trigram	X		X	X
EORTC QLQ-C30	X	X	X	X
EORTC QLQ-BR23	X	X	X	X
International Fitness Scale	X		X	X
Brief Pain Inventory short form	X	X	X	X
Hospital Anxiety and Depression Scale	X		X	X
Visual Analogue Scale for pain	X		X	X
Algometry	X		X	X
Body composition	X		X	X
Handgrip strength	X		X	X
Back muscle strength	X		X	X
Multiple sit-to-stand test	X		X	X
Abdominal test	X		X	X
6-min walk test	X		X	X
Borg Fatigue Scale	X		X	X
Accelerometry (1 week)	X		X	X
*Questionnaire to be completed at home after accelerometry*				
Questionnaire	X		X	X
IPAQ-SF Satisfaction survey			X	

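### The main ANCOVA fixes four covariates without the outcome's baseline value and leaves baseline's role in the group × time term unstated; either reading is less precise than a baseline-adjusted ANCOVA

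*Protocol article*

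**What the plan says.** The Data analysis section of the protocol article names the method: "For the main analysis we will use an analysis of covariance (ANCOVA) to assess the effects of intervention on study variables". It then gives the covariates as a definite list: "Time since diagnosis, age, tumor stage, and type of oncology surgery treatment will be used as covariates". The baseline value of the outcome is not on it.

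Baseline data appear in that section in two stated uses, as descriptive summaries and as a between-group comparison: "In a first step, we will analyze possible differences between groups at baseline using a one-way analysis of variance for continuous data". No consequence for the model is attached to that comparison. The section closes with a second analytic element: "To complete the analysis we will report effect size and level significance attending to interaction effects (group × time"). It does not say whether baseline is one of the levels of time.

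The baseline scores exist and are suitable as covariates. Under Research design and methods: "A randomized controlled trial will be conducted with assessments at baseline, 4 weeks and immediately after intervention (at 8 weeks"). Table 1 there schedules both primary questionnaires at baseline, 4 weeks, 8 weeks and the detraining visit. The Randomization and blinding section has the allocation envelopes opened only once baseline assessment is complete, so the baseline score cannot be affected by treatment.

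**The concern.** For a repeated questionnaire score, the earlier value of the same score is usually the strongest predictor of the later one. Age, time since diagnosis, stage and type of surgery do not stand in for it. A list that names four other variables and leaves this one out fixes a less efficient model than the data allow.

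Two things are at stake. The first is precision, in a trial that plans for 36 evaluable women per group. The second is chance imbalance between the groups at baseline: the plan tests for it but says nothing about correcting for it. Because the two possible readings of the model respond to such an imbalance in opposite directions, leaving baseline's role open also leaves room to choose after the data are seen.

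**Working it through.** **Inputs.** From the Sample size section: "we can detect differences of at least 5% with a power of 90% and an α of 0.05" (read as 5 points on the 0 to 100 scale), with two groups "of 36 participants assuming similar standard deviation of approximately 7 points", and 10% loss, giving 40 per group. Assumptions, because the article is silent:
- the correlation r between baseline and follow-up;
- equal SD at the two times;
- the SD of 7 is that of a single score, not of a change;
- a two-sided test.

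**Step 1: the plan's own figure.** n per group = 2(z₁ + z₂)² × SD² / difference², where z₁ is the normal quantile for α and z₂ that for power.
- Two-sided 0.05: 2 × (1.960 + 1.282)² × 49/25 = 41.2, so 42 (43 with the t distribution).
- One-sided 0.05: 2 × (1.645 + 1.282)² × 49/25 = 33.6, so 34 (35 with the t distribution).
- Dropout: 36/0.9 = 40 per group, 80 in total, as stated.

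The stated 36 is therefore close to the one-sided result. With 36 per group, noncentral t power is 84.8% two-sided and 91.2% one-sided.

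**Step 2: variance under each reading**, in units of the single-score variance:
- follow-up score only: 1;
- change from baseline, which is what a group × time contrast of week 8 with baseline amounts to: 2(1 − r);
- ANCOVA with the baseline score: 1 − r².

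The saving from adding baseline is r² against follow-up only. Against change it is 1 − (1 − r²)/(2(1 − r)) = (1 − r)/2. Equivalently, the change contrast has 2/(1 + r) times the variance of baseline-adjusted ANCOVA, which exceeds 1 for every r below 1.

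**Step 3: power**, for 5 points, SD 7, 36 per group, two-sided 0.05, noncentral t:

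| r | Saving vs follow-up only | Saving vs change | Power, follow-up only | Power, change | Power, baseline-adjusted |
|---|---|---|---|---|---|
| 0.3 | 9% | 35% | 84.8% | 71.4% | 88.0% |
| 0.5 | 25% | 25% | 84.8% | 84.8% | 93.2% |
| 0.6 | 36% | 20% | 84.8% | 91.6% | 96.2% |
| 0.7 | 49% | 15% | 84.8% | 97.1% | 98.7% |
| 0.8 | 64% | 10% | 84.8% | 99.7% | 99.9% |

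These savings ignore the four listed covariates. Any variance that those covariates share with the baseline score reduces the gain.

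**Step 4: chance imbalance.** The SE of the baseline difference is 7 × √(2/36) = 1.65 points. Suppose the groups differ at baseline by one SE.
- A follow-up-only estimate shifts by r × 1.65: +0.82 at r = 0.5 and +1.15 at r = 0.7.
- A change estimate shifts by −(1 − r) × 1.65: −0.82 at r = 0.5 and −0.49 at r = 0.7.

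Both compare with a 5-point target. Adjusting for the baseline score removes this shift, up to error in estimating the slope.

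**The case against.** The strongest reply is that the group × time sentence points to a repeated-measures model with baseline as the first level of time. If baseline were not a level, the interaction would test only whether the group difference varies across follow-up visits, which is not the treatment effect. On that reading baseline is used, and the loss is (1 − r)/2, which shrinks as r rises: at r = 0.7 the power gain is under 2 percentage points. This limits the size of the point but does not remove it. The article does not state this reading, and a change contrast is still less precise than baseline-adjusted ANCOVA and over-corrects for imbalance.

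It may also be said that this is a condensed article and a fuller analysis plan may say how baseline enters. That is fair as regards the time factor, so the article does not show that baseline is ignored. It does not cover the covariate list, which the article itself fixes.

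Four stronger readings are tempting, and the document does not support them:
- **That a quarter to a half of the residual variance is lost.** This holds only for a follow-up-only model with r between 0.5 and 0.7, and the article gives no r.
- **That the treatment estimate is biased.** Randomization keeps it unbiased on average, and its standard error already allows for chance imbalance.
- **That the trial is shown to be short of its 90% power.** The 84.8% rests on a two-sided test; sidedness is not stated, and a one-sided test gives 91.2%. This is a separate question. The SD is also not identified as that of a score or of a change. If it is the SD of change, the change contrast has 84.8% power and baseline adjustment brings it to 93.2% (r = 0.5) or 90.0% (r = 0.7), and the 1.65-point SE no longer follows in general.
- **That the model must include the randomization cycles.** The article says only that allocation was done "in five randomization cycles, using computer-generated numbers". It does not say that the cycles were strata or blocks, and they may have been recruitment batches.

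**Conclusion.** The point stands in a limited form. The covariate list is explicit, omits the outcome's baseline value, and leaves its role in the group × time term unstated. Under both readings the model is less precise than a baseline-adjusted ANCOVA, and chance baseline imbalance is not properly corrected.

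The direction does not depend on r, provided that baseline and follow-up are positively correlated (r below 1) and that the listed covariates do not already carry the same information. The size does depend on r. At r = 0.5 to 0.7, with the Step 3 assumptions, the gain in power is about 8 to 14 percentage points against a follow-up-only model, and about 8 down to under 2 points against a change contrast. It is an efficiency and pre-specification issue that should be put right; it does not threaten the validity of the comparison.

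**What to change.** State in the Data analysis section that each outcome at week 8 and at the final visit is analysed by ANCOVA with group, the baseline value of that outcome and the four covariates already listed, and that the adjusted mean difference is reported with its 95% CI. If the group × time result is kept, say whether baseline is a level of time and that the baseline-adjusted difference is the main result. No randomization-cycle factor is needed on what the article shows.

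The cost is a sentence or two of text and one degree of freedom per model. For every outcome that Table 1 schedules at baseline, no extra data, visits or patients are required.

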## Methods

### Objectives

The overall objective of the e-CUIDATE telerehabilitation randomized controlled trial is to evaluate the immediate and long-term effects of a telerehabilitation program on the overall impact of QoL, pain, body composition, physical measurement, cardiorespiratory fitness, fatigue, anxiety and depression, cognitive function, and lymphedema. The intervention group will receive three training sessions each week for an 8-week period. We will also study the effect of a 24-week period without telehealth support on the studied variables.We hypothesize that a strategy for care based on telerehabilitation to promote therapeutic exercise will increase QoL, reduce musculoskeletal disorders, and improve fitness in breast cancer patients.

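### The plan ties effect size and significance to the group × time interaction, which is neither the two-group difference the trial is sized on nor an estimate of the 8-week or long-term effect

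*Protocol article*

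**What the plan says.** All references are to the protocol article.

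- **Data analysis, model:** "For the main analysis we will use an analysis of covariance (ANCOVA) to assess the effects of intervention on study variables". No visit or contrast is attached to it.
- **Data analysis, covariates:** "Time since diagnosis, age, tumor stage, and type of oncology surgery treatment will be used as covariates". The baseline score of the outcome is not in the list.
- **Data analysis, inference:** "To complete the analysis we will report effect size and level significance attending to interaction effects (group × time". This is the only criterion given for judging the intervention effect. Means and standard deviations are also promised for each measurement occasion.
- **Objectives:** the aim is to "evaluate the immediate and long-term effects of a telerehabilitation program". The Abstract likewise names 8 weeks and 6 months, and ranks neither above the other.
- **Research design and methods:** "assessments at baseline, 4 weeks and immediately after intervention (at 8 weeks"), and then "Follow-up measurements will be carried out 24 weeks after the end of the 8-week intervention period". The Table 1 row for the primary instrument reads "EORTC QLQ-C30 X X X X", that is, all four visits.
- **Sample size:** one comparison of two groups on overall HRQoL, with a difference of 5 (written as a percentage, read here as points), SD about 7, power 90%, α 0.05, 36 per group and 40 after a 10% loss. No visit, between-visit correlation or repeated-measures term appears.

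**The concern.** Three parts of the article describe different questions. The objectives ask how large the effect is just after the programme and how much remains later. The sample size assumes one difference in means. The stated inferential criterion asks whether the two arms' profiles over time fail to be parallel.

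A significant interaction over four visits does not say at which visit the arms differ, or in which direction. An effect size attached to it is not a between-group difference in points, so it cannot be set against the 5 to 10 point minimally important difference that the Sample size section cites. A report could therefore declare the programme effective from an interaction driven by week 4 or by the last visit alone. The 90% power claim also does not describe the test from which significance would be read.

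**Working it through.** **Inputs from the article.** 36 per arm, difference 5 points, SD 7, α 0.05, and four QLQ-C30 visits.

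**Assumptions, not in the article.** SD 7 at every visit; the same correlation ρ between any two visits, taken as 0.3, 0.5 and 0.7; no difference at baseline; and the courses of effect listed below.

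**1. The plan's own figure.** For two means, n per arm = 2(z_α + z_β)² × SD²/Δ².
- One-sided: 2 × (1.645 + 1.282)² × 49/25 ≈ 33.6, so 34 (35 with the t distribution). This is within two of the stated 36.
- Two-sided: 2 × (1.960 + 1.282)² × 49/25 ≈ 41.2, so 42 (43 with t).
- Dropout: 36/(1 − 0.10) = 40 per arm, as stated.

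The figure is that of a single two-group comparison. The article does not state sidedness, and the present point does not depend on it.

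**2. Degrees of freedom.** Sized test: 1. Group × time over four visits: (2 − 1)(4 − 1) = 3.

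**3. Power of the interaction.** Let d_t be the between-group difference at visit t and d̄ its mean over the four visits. The noncentrality is λ = (n/2) × Σ(d_t − d̄)² / [SD²(1 − ρ)], with n/2 = 18. Power comes from the noncentral F with 3 numerator df. The denominator df is 68 for the multivariate test and 210 for the univariate test under sphericity, which gives the ranges below.
- Differences 0, 2.5, 5, 2.5: Σ(d_t − d̄)² = 12.5. At ρ = 0.5, λ = 18 × 12.5/24.5 = 9.18. At ρ = 0.3, λ = 225/34.3 = 6.56.
- Differences 0, 0, 5, 0: Σ(d_t − d̄)² = 18.75. At ρ = 0.5, λ = 337.5/24.5 = 13.8.
- Differences 0, 0, 0, 5, or 0, 5, 0, 0, or 0, 5, 5, 5: the sum is again 18.75, so λ and power are identical. Reversing the sign of every difference also leaves λ unchanged.

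**4. Power of a two-sided single-visit test of 5 points.**
- Unadjusted: SE = 7 × √(2/36) = 1.650, and 5/1.650 = 3.03 on 70 df gives 84.8%.
- Adjusted for the baseline score: the SD becomes 7 × √(1 − ρ²). At ρ = 0.5 this is 6.06, the ratio is 3.50 and power is 93.2%.

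| Test and course (weeks 4 / 8 / last visit) | ρ = 0.3 | ρ = 0.5 | ρ = 0.7 |
|---|---|---|---|
| Interaction, 2.5 / 5 / 2.5 | 53–55% | 69–71% | 91–92% |
| Interaction, 2.5 / 5 / 5 | 69–70% | 84–85% | 97–98% |
| Interaction, 5 / 5 / 5 | 73–75% | 87–88% | 98–99% |
| Interaction, 5 at week 8 only | 73–75% | 87–88% | 98–99% |
| Interaction, 5 at the last visit only | 73–75% | 87–88% | 98–99% |
| Single visit, unadjusted, 5 points | 84.8% | 84.8% | 84.8% |
| Single visit, baseline-adjusted, 5 points | 88.0% | 93.2% | 98.7% |

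**5. Reading.** The week-8-only and last-visit-only rows are identical. A test aimed at week 8 would reject 5% of the time when week 8 shows no effect. The interaction, at ρ = 0.5, rejects 87–88% of the time in that situation if 5 points exist only at the last visit.

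**The case against.** The strongest reply is that too much is being read into one sentence. ANCOVA is called the main analysis, and the interaction sentence opens as a completion of it, so the interaction may be only a supplement. The number of visits entering it is not written. An interaction over two visits has 1 df and a direction, and it equals the difference in change. Most secondary outcomes have no week-4 measurement. Means by visit will be reported, so direction will be visible. These points stand as limits: the four-visit, 3-df reading comes from the sentence taken together with Table 1 and is not stated. They do not remove the problem, because the ANCOVA has no visit or contrast and the interaction is the only criterion the article gives. Descriptive means also carry no interval or test.

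Three stronger readings are tempting and are not supported.

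- **That the interaction necessarily loses power.** The 88–99% comparator includes a baseline adjustment that the plan does not list. Against the unadjusted 84.8%, the interaction is about equal or better under several courses at ρ = 0.5, and better under every course shown at ρ = 0.7.
- **That women who miss a visit are dropped, and that this biases the week-8 effect.** The article names neither a repeated-measures complete-case analysis nor any missing-data rule. It only states "We will assume a maximum loss at follow-up of 10" per cent.
- **That week 8 is the primary time point.** The article gives the immediate and later effects equal standing. A difference at the last visit answers a stated objective.

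**Conclusion.** The point holds as a mismatch between the question, the sizing and the stated inferential criterion. On the most natural reading, significance for the primary instrument would come from a 3-df test whose rejection neither locates nor estimates the 8-week or long-term effect. At 36 per arm, SD 7 and ρ = 0.5, it rejects with the same 87–88% probability for an effect confined to week 8 and for one confined to the last visit. This equality holds at any common correlation; only the level depends on ρ.

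The power consequence is conditional. For a 2.5/5/2.5 course it runs from 53–55% to 91–92% over ρ = 0.3 to 0.7, and other courses do better. All power figures rest on equal SDs, a common correlation and assumed courses of effect, none of which the article supplies apart from the SD of about 7. The defect should be corrected, but it does not invalidate the design.

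**What to change.** Replace the interaction as the inferential result with the between-group difference in QLQ-C30 overall HRQoL at named visits, each with a 95% confidence interval. One arrangement is week 8 as primary and the final visit as key secondary. The sponsor should choose the order and state it.

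Obtain the differences from a mixed model over the post-baseline visits, or from an ANCOVA at each named visit. Either should adjust for the baseline score as well as the four listed covariates, and use all available data by randomized group. Keep the group × time p-value as supportive only. State in the Sample size section which visit and contrast the 36 per arm refers to.

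The cost is a change of analysis wording, slightly more modelling work and a commitment to one primary visit. Recruitment, assessments and treatment are unaffected. The Trial status section reports active recruitment, so the change can be recorded before results are seen.
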